## 1. Introduction

Dementia currently affects more than 47 million people worldwide, its prevalence is forecasted to triple by 2050, and it has been reported to be one of the most costly disorders in Belgium.

There is good scientific evidence that the cognitive impairments associated with the development of dementia can be lessened or even reversed thanks to the plasticity of the brain (rewiring). Recent research has shown that physical activity combined with performing cognitively challenging tasks is a very potent way to induce this rewiring of the brain, which can enable people to improve their cognitive functions. Yet, so far, these studies are mainly limited to controlled laboratory conditions. Our team developed a real-life cognitively enriched walking program, with input from experts and end-users.

In this study, we will examine the added value of enriching physical activity (walking) with cognitive exercises in improving cognition of older adults by conducting a six-month community-based randomized controlled trial. We will also examine the longer term effectiveness in a follow-up measurement visit six months after the program. We will focus on the following outcomes: cognitive functioning (i.e., objective, subjective and cognitive activity), psychosocial wellbeing (i.e., loneliness, social support, depressive symptomatology, positive wellbeing and expectations regarding aging), physical activity (i.e. both objective and subjective) and general health.

## 2. Study design

To evaluate the effects of the cognitively enriched walking program on cognitive functioning (primary outcome), physical activity and psychosocial wellbeing (secondary outcomes), a randomized controlled trial (RCT) will be conducted. The intervention period will be 6 months, with measurements conducted at baseline, 3 months (mid-intervention), 6 months (post-intervention) and 12 months (follow-up). The interventions and measurements will take place at 2 university campuses in Belgium (Ghent and Leuven).

Participants will be allocated to one of the following intervention arms with a 1:1:1 allocation ratio: (1) cognitively enriched walking program, (2) walking program without enrichment, (3) passive control group. An investigator not involved in running the trial will generate the randomization sequence stratified by location (Ghent/Leuven) and availability (2 scheduling options for each location) using a statistical software program. Allocation will be disclosed to the researchers and participants only after completion of baseline measurements, ensuring double-blind data collection at baseline.

Furthermore, a process evaluation will be embedded in the RCT, using a mixed-methods design, and thus comprises questionnaires and focus group interviews. Questionnaires will be completed mid-intervention and post-intervention, focus groups will be conducted post-intervention.

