## 5. Outcome measures

### 5.1. Effectiveness

The main outcome of this study is cognitive functioning. We chose several outcome measures to assess different aspects of **cognitive functioning**.

- *Cambridge Neuropsychological Test Automated Battery (CANTAB)* (Bento-Torres et al., 2017; Sahakian & Owen, 1992; Zygouris & Tsolaki, 2015): objective cognitive functioning is assessed with CANTAB.

Different tests can be configured in a test battery, based on the focus of the study. The tests are non-verbal and culturally independent and make use of touchscreen technology. The CANTAB has been shown sensitive to changes in cognitive performance. Six different tests were selected to obtain a comprehensive view of one's objective cognitive functioning. The selected tests assess psychomotor speed/attention (i.e. sustained attention), memory (i.e. visual episodic attention and short term visual memory) and executive functioning (i.e. working memory and strategy). This is the primary endpoint of the study

- *Cognitive and Leisure Activities Scale (CLAS)* (Galvin et al., 2021): this is a measure of the type and frequency of cognitive activities. It includes sixteen types of cognitive activities and is self-administered. Even though it is difficult to establish the validity of this new questionnaire since there is no gold standard to measure cognitive activity, it is suggested that this questionnaire has a good content validity. This will be used as a covariate in the analysis.
- *Cognitive Failures Questionnaire (CFQ)* (Broadbent et al., 1982; Ponds et al., 2006): this self-administered questionnaire assesses subjective cognitive functioning. Participants are asked about minor everyday slips or errors. It is not a replacement for testing objective cognitive functioning, but reflects the experience of the frequency of everyday slips of the participant.

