### Focus groups

All participants of the PA only and PA+CA groups will be invited to participate in focus groups. In total, there are four groups performing the PA only program (two in Leuven and two in Ghent) and four groups performing the PA+CA program (two in Leuven and two in Ghent). We will organize eight focus groups for participants, one for each group. Each focus group will consist of 8-13 participants.

There are four coaches guiding the PA only groups and four coaches guiding the PA+CA groups. Therefore, we opted to organize one focus group for the coaches of the PA only groups (from both Ghent and Leuven) and one focus group for the coaches of the PA+CA groups (from both Ghent and Leuven). Each focus group for coaches will thus consist of 4 participants.

Every focus group will take around 60-90 minutes. Focus groups for participants will be organized on campus (in Ghent or Leuven, depending on where participants were part of an intervention group). Focus groups for coaches will be organized on a KU Leuven campus in Brussels (because coaches from Ghent and Leuven will participate in the same focus group). For all focus groups, a semi-structured interview guide will be used. In total, four separate interview guides are prepared: 1) coaches of the PA only groups, 2) coaches of the PA+CA groups, 3) participants of the PA only groups, 4) participants of the PA+CA groups. The PhD student will be moderator of all focus groups, the postdoctoral researcher and/or a master student will be observer. All focus groups will be audio-recorded, and the observer will take notes during the focus groups. The interview guides are attached as additional file 3, 4, 5 and 6.

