### **Three months visit**

Three months after the start of the intervention, participants will be invited for a second visit. Again they will be asked to complete the questionnaires regarding cognitive function, psychosocial wellbeing, physical activity and general health. The CANTAB will be administered and they will be asked to wear the accelerometer for seven consecutive days. This measurement visit will take place during the intervention period for the PA+CA and PA groups, this will be taken into account in the analysis of the accelerometer data. Furthermore, a process evaluation questionnaire will be given to participants of the PA+CA and PA groups. This questionnaire can be completed at home and returned during the next (cognitively enriched) walking session. Accelerometers can be delivered to the office of one of the researchers or returned by post (pre-paid by the research team).

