## 6. Statistical analysis plan

### 6.1. Hypotheses

#### Primary endpoint:

We hypothesize that the cognitively enriched walking program will have more beneficial effects on cognitive functioning compared to the other conditions at 6 months and 12 months.

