#### Primary outcome

For each cognitive test used, a selection of outcome measures will be used based on literature. Next, composite scores will be constructed for short-term memory (STM), long-term memory (LTM), executive functioning (EF) and processing speed (PS). The procedure for this is described below

The outcome measures, categorized by cognitive function:

| Short-term memory (STM)                           | Long-term memory (LTM)                          | Executive functioning (EF)                             | Processing speed (PS)        |
|---------------------------------------------------|-------------------------------------------------|--------------------------------------------------------|------------------------------|
| VRM free recall distinct stimuli (VRMFRDS)        | VRM delayed recognition total correct (VRMDRTC) | SWM strategy (SWMSX)                                   | RTI reaction time (RTIFMDRT) |
| VRM immediate recognition total correct (VRMIRTC) |                                                 | SWM between errors levels 4, 6, 8 and 12 (SWMBE46812)* |                              |
| PAL first attempt memory score (PALFAMS28)        |                                                 | OTS problems solved upon first choice (OTSPSFC)        |                              |
| PAL total errors (PALTEA28)                       |                                                 |                                                        |                              |
| DMS percentage correct (DMSPCAD)                  |                                                 |                                                        |                              |

\*SWMBE46812 is calculated by summing SWMBE4, SWMBE6, SWMBE8, SWMBE12

*STEP 1:* Create z-scores based on the pooled mean (across conditions), separately for each time point

*STEP 2:* Reverse-score the z-scores for the following outcome measures:

PALTEA

SWMSX

SWMBE46812

RTIFMDRT

*STEP 3:* Calculate the composite scores using the following formulas

$STM = (VRMDRDS + VRMIRC + PALFAMS28 + PALTEA28 + DMSPCAD)/5$

$LTM = VRMDRTC$

$EF = (SWMSX + SWMBE46812 + OTSPSFC)/3$

$PS = RTIFMDRT$

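### The plan ends blinding for the researchers after baseline and does not mask whoever administers CANTAB at 3, 6 and 12 months

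*Combined protocol and SAP*

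**What the plan says.** **Disclosure.** Section 2 covers blinding in one sentence: "Allocation will be disclosed to the researchers and participants only after completion of baseline measurements, ensuring double-blind data collection at baseline". It does not define who the researchers are and exempts nobody.

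**Endpoint and timing.** Of CANTAB, section 5.1 says "This is the primary endpoint of the study". Section 6.1 expects the enriched programme to have "more beneficial effects on cognitive functioning compared to the other conditions at 6 months and 12 months".

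**Follow-up visits.** For the three-month visit, section 5.3 says "The CANTAB will be administered and they will be asked to wear the accelerometer for seven consecutive days", in the passive voice and without naming a tester. The six- and twelve-month visits follow the same procedure, except that the twelve-month visit has no process questionnaire.

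**Arm-dependent steps.** At three months, and by the same procedure at six, "Furthermore, a process evaluation questionnaire will be given to participants of the PA+CA and PA groups". The Questionnaires part of section 5.2 describes separate versions for the two walking programmes, delivered by an online link. Focus groups are held after the intervention, one per walking group: "The PhD student will be moderator of all focus groups, the postdoctoral researcher and/or a master student will be observer".

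**Mode of testing.** Section 5.1 describes the battery thus: "The tests are non-verbal and culturally independent and make use of touchscreen technology".

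**The concern.** Blinding at baseline protects the comparability of the starting values. It does nothing for the contrast that the trial is designed to estimate, which arises only after disclosure. The team developed the enriched programme, and the primary hypothesis favours it. A tester who knows the arm can differ, without intending to, in how instructions are explained, how much encouragement is given, and how fatigue or interruptions are handled. If such differences follow the arm, they enter the primary comparison as bias, which the mixed model cannot detect and a larger sample cannot reduce. Participants in a walking trial cannot be masked, but testers can be, at least in part.

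**Working it through.** **Step 1: is masking restored anywhere?** The plan gives no figure to reproduce, so the check is to set the relevant sections side by side.

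| Visit | Relation to disclosure | Masking of tester | Step that depends on arm |
|---|---|---|---|
| Baseline | Before | Claimed (section 2) | None |
| 3 months | After | Not mentioned | Process questionnaire, walking arms only |
| 6 months | After | Not mentioned | Same as 3 months |
| 12 months | After | Not mentioned | None at the visit |

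No section provides a masked assessor, separate testing staff, or a request that participants keep their group to themselves.

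**Step 2: how firm is it that testers know the arm?**

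- Section 2 discloses allocation to the researchers without exception, and at the baseline visit participants put their questions to a researcher. If the same people test at follow-up, they know the arm.
- At 3 and 6 months, anyone who hands over the questionnaire learns that the participant is in a walking arm. The version shows which one.
- The focus groups bring the PhD student, and the postdoctoral researcher and/or a master student, face to face with participants by arm. The groups come after the intervention. That they precede the 12-month visit is likely but not stated.

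This supports a strong inference, but no sentence states it as fact. For 12 months it rests on the disclosure rule, the likely order of the focus groups, and the absence of any masking provision.

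**Step 3: what would a small systematic shift do?** The shifts below are assumptions; the documents give none.

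- Evaluable participants: 124 (section 6.2). With 1:1:1 allocation (section 2), 124/3 = 41.3, taken as n = 41 per arm.
- α = 0.05 (section 6.4), taken as two-sided because the plan does not say.
- Outcome in SD units, no true effect, one unadjusted comparison of two arms: SE = √(2/41) = 0.221.
- For a shift of b SD: P(reject) = 1 − Φ(1.96 − b/SE) + Φ(−1.96 − b/SE).
- Example, b = 0.10: b/SE = 0.453, so 1 − Φ(1.507) + Φ(−2.413) = 0.066 + 0.008 = 0.074.

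| Assumed shift b (SD) | b/SE | P(reject), no true effect |
|---|---|---|
| 0 | 0 | 5.0% |
| 0.05 | 0.226 | 5.6% |
| 0.10 | 0.453 | 7.4% |
| 0.15 | 0.679 | 10.4% |
| 0.20 | 0.906 | 14.8% |

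With 50 per arm (149/3 = 49.7, no dropout), shifts of 0.10 and 0.20 SD give 7.9% and 17.0%. More participants make the problem slightly worse, because bias does not shrink with n. The planned mixed model will have a different standard error, and the plan corrects post-hoc p-values. The table shows sensitivity only and does not estimate the bias in this trial.

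**The case against.** The strongest reply is that the endpoint is largely protected by its mode. The only description of the tests calls them non-verbal and touchscreen-based, which leaves a tester little room to influence the score. Participants know their arm and perform the tests themselves, so expectation effects would persist even with a perfectly masked tester. Both points stand. They limit the likely size of the bias and the benefit of masking. They do not remove the tester's part in instruction and encouragement, and the sponsor thought blinding worth claiming at baseline with the same battery.

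A reader might infer more than the documents support:

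- *That follow-up tests are in fact run by staff who know the arm.* The tester is never named, and the group called researchers is not defined.
- *That the visit itself must unmask the tester.* The three-month section does not say who hands over the questionnaire, the Questionnaires section describes an online link, and there is no questionnaire at 12 months.
- *That examiners record free recall by hand, so this score in the short-term memory composite is especially exposed.* Section 6.4 gives only the name of the measure. Nothing says how it is recorded or scored.
- *That the bias can be put at some share of the planned effect of 0.30.* That would need a shift on a given test and a correlation between tests, neither of which the documents give. Section 6.2 also does not say whether 0.30 is a standardised mean difference or another metric.
- *That a positive result would be uninterpretable.* With the size unknown and touchscreen tests in use, that goes too far.

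**Conclusion.** The gap is certain: as written, the plan discloses allocation to the researchers after baseline and masks nobody who administers the primary endpoint at the visits that its hypothesis concerns. That testers will know the arm is a strong inference from the disclosure rule, the arm-dependent steps and the team's role in the focus groups. The direction of concern is towards the enriched programme. The size is unknown, and the documents allow no estimate. The false-positive rates of 5.6% to 14.8% depend wholly on assumed shifts of 0.05 to 0.20 SD and a simple two-arm comparison with 41 per arm. They show only that modest shifts matter at this sample size. The plan should be changed because this source of bias is avoidable at low cost. If the sponsor already intends masked testers, the same passages still need to say so.

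**What to change.** 1. In section 2, limit disclosure to the team members who need it: those who send allocation letters, liaise with coaches or run focus groups.
2. In section 5.3, state that CANTAB at 3, 6 and 12 months is administered by existing team members without access to the allocation list.
3. Align this with the focus groups. The PhD student moderates all of them and so cannot be a masked tester at 12 months, nor at 6 months for anyone whose focus group comes first. Whichever of the postdoctoral researcher or master student tests at 12 months should not observe focus groups. The current wording on observers allows that.
4. Ask participants before each test visit not to mention their group.
5. Deliver the process questionnaire through the online link instead of at the test visit. This also reconciles the Questionnaires section with the three- and six-month visit sections, which describe a form to be handed in or posted back.
6. Record every unblinding, with visit and reason.
7. Where existing staff cannot cover a visit masked, state that the visit is unblinded and interpret its result accordingly.

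The cost is protocol wording and a staff rota. Sample size, visits and tests do not change, and no new staff are presumed, because item 7 covers visits that cannot be staffed. The downsides are scheduling effort across two campuses and incomplete masking, since some participants will still reveal their arm.

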## 3. Participants

### 3.1. Recruitment

Participants for this study will be recruited by convenience and snowball sampling. Flyers with basic information on the study, the researcher's contact information (i.e. e-mail address and phone number), and name of the study's website will be distributed through different channels. Examples of these channels are local service centres, community health centres, stakeholders and organisations for older adults (e.g. OKRA, Vief, S-plus, Vlaamse Ouderenraad), social media and mail to people who previously showed interest in this program and provided their contact details (e.g. people that were not selected for participation in the pilot study but agreed to be kept informed about this study, people reached through an information day (Care4Brain) of the Leuven Brain Institute). On the website, we will share a brief summary of what is expected of study participants. Furthermore, our in- and exclusion criteria as well as our contact information will be listed on the website. It will also be stated that during an initial phone call, the in- and exclusion criteria will be discussed and that only with participants meeting these criteria, an appointment will be made for the baseline measurement. We will also try to specifically reach neighbourhoods of people with lower socioeconomic status, because these people are often less physically active. We will do this by distributing our flyers in community (health) centres in person, to have

a first personal contact with our potential participants. Furthermore, an advertisement will be placed in a local newspaper and/or on Facebook and we will organize live information sessions for all those interested. To ensure the handed information is understandable for everyone, we will use no specialist terms on our flyers or website.

We will also recruit coaches, who will supervise the sessions. These coaches will be hired, and thus paid, for their contribution to this project. To recruit them, will contact Wandelsport Vlaanderen saying that we are looking for certified walking coaches for this particular project, including a flyer that can be distributed. They will then contact the suited walking initiators and let us know who is interested in this project. By certified, we mean that the coaches have completed the training 'walking initiator' of Wandelsport Vlaanderen and Vlaamse Trainersschool.

### 3.2. Inclusion and exclusion criteria

We will include male and female volunteers aged 65 years and older. The age of 65 years is a well-accepted cut-off as well as the age at which most people can retire in Belgium. This means that people of this age group will be more likely to have enough free time to participate in this study. Participants have to be community-dwelling.

Because we aim to investigate the effects of the cognitively enriched walking program on cognitive function of healthy older adults, potential participants will be excluded if (they):

- (1) Have a neurodegenerative disorder (i.e. Alzheimer's disease, Parkinson's disease, Multiple Sclerosis,...);
- (2) Are diagnosed with mild cognitive impairment (MCI);
- (3) Are diagnosed with a psychiatric disorder (e.g. schizophrenia, bipolar disorder, borderline personality disorder,...);
- (4) Are currently having a depressive episode;
- (5) Have had a serious brain injury in the past year, or before and still experience consequences (i.e. traumatic brain injury, stroke, brain haemorrhage);
- (6) Have a history of, or current, addiction to drugs or excessive alcohol abuse;
- (7) Are not able to walk approximately three kilometres in one hour (at an average walking pace);
- (8) Make use of a walking aid (i.e. a cane, a (rollator) walker, or a wheelchair);
- (9) One or both of their parents were diagnosed with juvenile dementia;
- (10) Know in advance that they will not be will not be present for one or more periods of longer than one month (e.g. because of a long holiday).

### 3.3. Screening

Since the focus of this study is evaluating this program in cognitively and physically healthy older adults and cognitive functioning is our primary outcome, we decided to add two objective criteria to exclude participants that are more likely to have cognitive impairment. Firstly, participants with a score of less than 23 on the Montreal Cognitive Assessment tool (MoCA) will be excluded, as this might indicate (the beginning of) mild cognitive impairment (Carson et al., 2018). Additionally, we will exclude participants with a score of 20 and above (i.e. moderate to severe depression symptoms (Balsamo et al., 2018) on the Beck Depression Inventory (BDI-II), as depression can impact cognitive functioning (Köhler et al., 2010). Whenever participants are excluded because of a MoCA score below or BDI-II score above the cut-off, the participant will be informed about the deviant score by the either the PhD student (who has a MSc in Psychology and did an eight-month internship at a geriatric's department) or the postdoctoral researcher (who has a MSc and PhD in Psychology, took a course in psychogeriatrics, worked at a geriatric's department and works part-time as a primary care psychologist). Furthermore, the person will receive a letter that they can bring at their next appointment with their general practitioner. The letter will (1) contain the description of the test and the score obtained and an explanation that there are multiple possible reasons for such a score, and that only one of them is (mild) cognitive impairment or depressive symptomatology and (2) indicate that, in case the general practitioner thinks this is necessary, an appointment can be made with a memory clinic or psychologist.

